##### Recruitment

Where appropriate consultants, nurses, or MCRN/CRC Cymru research nurses will send an information pack to a child/young person (and if under 16 years their parent/guardian) attending a clinic one week prior to the clinical appointment. During the clinic visit, the consultant/nurse/research nurse will ask them if they want to take part in the study. If the child/young person agrees to take part in the study, the consultant/nurse/research nurse will take the consent from young people over 16 years, assent and parent/guardian proxy consent from children under 16 years. Children and young people not entered into the trial will receive standard care.

##### Allocation

Children age 6-18 years fulfilling the inclusion criteria and for whom appropriate consent(s) (proxy if appropriate) are obtained will be randomized using an independent web based randomisation service supported by the North Wales Organisation for Randomised Controlled Trials in Health and Social Care (NWORTH).

##### Randomisation

A web-based, password protected, secure adaptive randomisation with a telephone backup has been developed.

168 children/young people will be randomized into the intervention arm and 84 children/young people into the no intervention arm, stratified by gender, length of time since diagnosis (< 2 years and > 2 years) and age (stratification by age will be into the following age categories: 6-10 years; 11-15 years; and 16-18 years).

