### Stage 3. Trial platform to evaluate the diabetes diaries and information packs in routine practice

#### Methods

##### Study design

This trial is an individually randomised controlled trial with two parallel groups. The protocol is summarised in Figure 1.

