##### Site selection and preparation

Depending on the size of site and number of children/young people with diabetes type 1, we envisage up to 10 sites (depending on current NHS re-organisation and amalgamation of Trusts) will recruit children and young people. We will be guided by co-applicant clinicians and the MCRN/CRC Cymru research network who have an overall view of available of sites for trials and will have an overall strategic role in supporting research teams to facilitate site and participant recruitment [38].

The age-appropriate diabetes diaries and information pack will be individually-tailored and introduced by nurses/doctors in children and young people's diabetes clinics during routine visits. We will hold a launch event to familiarise healthcare professionals with the information pack in each participating site.

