#### Planned interventions

##### Group 1 - Information intervention

An age-appropriate diabetes diary and information pack produced or assembled for the study will be selected and individually-tailored as appropriate to each child/young person depending on their age and diabetes management, and introduced by nurses/doctors and as appropriate other multi-disciplinary team members in clinic during routine visits by children/young people between the ages of 6-18 years with type 1 diabetes. Parents of children under 16 years will be provided with verbal and written guidance on supporting their child's use of the information pack. Parents attending clinic consultations with young people over 16 years will receive the same verbal advice as the young person, and written guidance will be aimed at the young person.

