##### Group 2-Standard practice

Children age 6-18 years with type 1 diabetes receiving standard practice will be the 'practice as usual' control group. A manual of standard practice for each centre will be produced. This will help with the comparisons of outcomes at the end of the trial.

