#### Data analysis

##### Statistical analysis

Initial descriptive statistics will describe characteristics and demographics of the sample at baseline. We shall compare outcomes between the two groups by analysis of covariance to adjust for possible differences in baseline measurements. This will be repeated at 3 and 6 months comparing intervention and control groups. In addition, longitudinal analysis will consider any changes over time. These analyses will examine changes in the quality of life measures (paediatric EQ-5D, PedsQL generic and diabetes-specific health measures) over baseline, both using a pairwise comparison, studying change on individuals, and a cohort analysis comparing overall change in group means.

Multiple regression analyses will be performed to identify factors which predict good outcomes within and between groups.

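### Centre is not a factor in the adaptive randomisation, although up to 10 clinics deliver both arms under 2:1 allocation: a cheap improvement in balance and precision

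*Protocol article*

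**What the plan says.** The Randomisation section describes the system as already built: "A web-based, password protected, secure adaptive randomisation with a telephone backup has been developed". The 168 intervention and 84 control places are "stratified by gender, length of time since diagnosis (< 2 years and > 2 years) and age". The abstract and the section on sample size and effect size name the same three factors. None of the three places names centre or site.

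Other sections show why centre matters in this trial:
- Study design: "This trial is an individually randomised controlled trial with two parallel groups". Children in one clinic can therefore fall in either arm.
- Site selection and preparation: "we envisage up to 10 sites (depending on current NHS re-organisation and amalgamation of Trusts) will recruit children and young people".
- Group 1: the pack is "introduced by nurses/doctors and as appropriate other multi-disciplinary team members in clinic during routine visits", that is, by local staff.
- Group 2: "A manual of standard practice for each centre will be produced", to help in comparing outcomes when the trial ends.
- Statistical analysis: "We shall compare outcomes between the two groups by analysis of covariance to adjust for possible differences in baseline measurements". Centre is neither named nor ruled out.

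**The concern.** The control condition is whatever each clinic normally does, and the protocol expects this to differ enough to document it clinic by clinic. Delivery of the pack also depends on local staff. The scheme balances three patient characteristics but not this structural factor.

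With 2:1 allocation and about 25 children per site, the proportion of controls can vary considerably between sites. Any difference in outcome between centres then adds noise to the arm contrast. A later analysis plan can add a model term, but it cannot change how children were allocated. The balancing factors therefore have to be right before the first child is randomised.

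**Working it through.** **Inputs from the protocol:** effect size 0.4; 80% power at the 0.05 level (quoted for the cited review's calculation; two-sided assumed); 10% dropout; 2:1 allocation; 252 children (168 and 84); up to 10 sites. **Assumed, because the protocol gives no figures:** 10 equal sites; share of outcome variance due to centre (ICC) from 0.01 to 0.10.

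**1. The plan's own figure.** Controls needed = (1 + 1/2) × (1.960 + 0.842)² / 0.4² = 1.5 × 7.85 / 0.16 = 73.6, rounded up to 74, so 222 in total. Then 222 / 0.9 = 246.7, or 247. With the t distribution, 75 controls are needed; 75 / 0.9 = 83.3, rounded up to 84, and 84 × 3 = 252. The stated total is reproduced.

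**2. Split within a site.** 252 / 10 = 25.2 children per site. If allocation ignores site, the number of controls among 25 is approximately Binomial(25, 1/3). The mean is 8.3 and the 2.5 and 97.5 percentiles are 4 and 13; fixing the totals at 168 and 84 gives the same range. Across 10 sites (20,000 simulated allocations), the lowest site share on intervention has a median of 52% and the highest a median of 80%, against 67% planned.

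**3. Precision, ignoring the baseline score.** With centre balanced and adjusted for, the variance of the arm difference tends to (1 − ICC) times its value. With 84 × 0.9 = 75.6 controls analysed, power at 0.4 SD is 81.1% when centre is ignored. It becomes:

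| ICC | Power, centre balanced and adjusted for |
|---|---|
| 0.01 | 81.4% |
| 0.02 | 81.8% |
| 0.05 | 83.0% |
| 0.10 | 84.9% |

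At ICC 0.05 to 0.10 this is worth 0.05 × 252 = 12.6 to 0.10 × 252 = 25.2 children.

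**4. Precision with the planned baseline adjustment.** Stable centre differences already show in the baseline score, so the analysis of covariance removes part of them. I simulated 10 sites and 227 analysed children, with an assumed baseline-to-follow-up correlation of 0.6 within centres (12,000 runs per setting; simulation error in each ratio about 0.02). The ratio compares centre balanced and modelled with centre in neither, both adjusted for baseline:

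| ICC | Correlation of centre effects, baseline with follow-up | Variance ratio |
|---|---|---|
| 0.02 | 0.5 or 0.9 | 0.99 |
| 0.05 | 0.5 | 0.97 |
| 0.05 | 0.9 | 1.00 |
| 0.10 | 0.5 | 0.91 |
| 0.10 | 0.9 | 0.97 |

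The gain is thus about 0 to 9%. Only if centre differences at follow-up were wholly unrelated to those at baseline would it be larger (about 9% at ICC 0.05 and 16% at 0.10). That is unlikely over six months in the same clinics.

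**5. Error rates** (6,000 runs, no baseline covariate, same treatment effect in every centre, ICC 0.05 to 0.10). With centre in neither place, type I error is 4.5 to 5.1% and power 80 to 82%. With centre balanced but left out of the model, type I error is 4.3 to 4.5%, slightly conservative. With both, power is 83 to 84%.

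**6. Feasibility.** The existing factors make 2 × 2 × 3 = 12 cells. Crossing them with 10 centres gives 120 cells of 252 / 120 = 2.1 children, too few for crossed strata. An adaptive algorithm avoids this by taking centre as one more factor.

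**The case against.** The case against is that nothing is stated wrongly. Individual randomisation keeps the comparison unbiased, the 80% target is met with centre ignored, and the baseline covariate already absorbs much of any stable centre difference. All of this stands, and it limits the size of the point. It does not explain why centre is left out of a list that is explicit, given three times and built into the system.

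Some stronger readings are tempting, but the document does not support them:
- **That the analysis omits centre by decision.** The article names baseline adjustment only. Further covariates may sit in an analysis plan that is not shown, so this silence alone is no finding.
- **That adjustment in the analysis could achieve almost nothing by itself.** With a random intercept and no balancing, and before baseline adjustment, the variance ratio is about 0.975 at ICC 0.05 and 0.94 at 0.10. That is at least half of the available gain.
- **That small clinics will have almost no controls.** No site sizes are given. In a hypothetical 12-child site the chance of 0 or 1 controls is 5.4%, and of none 0.8%. In a site of 25 the chance of 0 or 1 is 0.05%.
- **That a planned centre-by-centre comparison is undermined.** The manuals are meant to help interpret outcomes; no such comparison is planned.
- **That laboratory differences distort the primary result.** The primary outcome is a questionnaire score. Laboratories bear only on HbA1c, a secondary outcome.
- **That type I error is inflated.** It reaches about 7.3% only if the treatment effect itself varies between centres with an assumed SD of 0.2, and a fixed centre term does not correct that.

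One objection bears on the remedy. Clinic staff both recruit and introduce the pack, so they see local allocations, and balancing within small sites makes the next allocation somewhat easier to guess.

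**Conclusion.** The point holds as a cheap improvement. Centre is missing from the balancing factors of a trial in which up to 10 clinics, with their own standard practice and staff, deliver both arms at 2:1. The comparison remains unbiased and 252 stands. What is lost is control over the split within sites (4 to 13 controls in a site of about 25) and some precision: roughly 0 to 10% of the variance of the arm difference after baseline adjustment at ICC 0.05 to 0.10. The loss is near zero at a lower ICC, or where centre differences are already visible at baseline. The figure of 12 to 25 children is therefore the upper end, not an expected saving. The results rest on assumed equal sites, ICC and correlations. The missing factor itself rests on the text alone.

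**What to change.** Before opening, add centre as a fourth factor in the existing adaptive algorithm, not as a crossed stratum. Keep the algorithm's random element, so that allocations within small sites stay hard to predict. Because centre is then a balancing factor, include it in the analysis of covariance for the primary outcome and for HbA1c, either as a random intercept or as a fixed effect with small sites pooled.

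The cost is one parameter in the randomisation system and one model term, with no change to the sample size. Balance on gender, time since diagnosis and age becomes slightly looser, and allocation within small sites slightly more predictable.

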#### Planned interventions

##### Group 1 - Information intervention

An age-appropriate diabetes diary and information pack produced or assembled for the study will be selected and individually-tailored as appropriate to each child/young person depending on their age and diabetes management, and introduced by nurses/doctors and as appropriate other multi-disciplinary team members in clinic during routine visits by children/young people between the ages of 6-18 years with type 1 diabetes. Parents of children under 16 years will be provided with verbal and written guidance on supporting their child's use of the information pack. Parents attending clinic consultations with young people over 16 years will receive the same verbal advice as the young person, and written guidance will be aimed at the young person.

##### Group 2-Standard practice

Children age 6-18 years with type 1 diabetes receiving standard practice will be the 'practice as usual' control group. A manual of standard practice for each centre will be produced. This will help with the comparisons of outcomes at the end of the trial.

#### Outcome measures

##### Primary outcome measures

Choice of outcomes is guided by a Health Technology Assessment commissioned systematic review recommending that HbA1c (glycaemic control measure) is not the appropriate primary outcome on which to assess benefits of an intervention designed to more directly effect behaviour/self-management [39]. Therefore, the primary outcome measure is diabetes self-efficacy and quality-of-life as measured by the single composite score derived from the Diabetes PedsQL.

##### Secondary outcome measures

Secondary outcomes include: HbA1c, generic quality of life, routinely collected NHS/child-held data, costs, service use, acceptability/utility.

#### Baseline, 3 and 6 month data collection

Children/young people (if appropriate with support of, or proxy report by parents) will complete a baseline questionnaire recording sociodemographic variables, patient characteristics, and PedsQL (generic, diabetes and parent versions). The EQ-5D will be completed by parents (as a proxy measure) as well as the child/young person.

Follow-up questionnaires, containing the same outcome measures as at baseline, and with an additional focus on process will be administered at 3 months and 6 months, (including data on health service use, episodes of diabetic ketoacidosis, and all hospital admissions for acute complications). Non-responders will receive telephone/postal reminders after two and four weeks.

Baseline and subsequent HbA1c measurements and routinely collected NHS/child-held data will be collected by the clinicians/diabetes nurse specialists/MCRN nurses, or researchers where appropriate. Blood glucose meters will be checked for the previous 250 blood glucose records if considered appropriate by the clinician and if used as part of routine clinical practice.

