**Methods/Design:**

We used published evidence, undertook qualitative research and consulted with children, young people and key stakeholders to design and produce a range of child-centred, age-appropriate children's diabetes diaries, carbohydrate recording sheets, and assembled child-centred, age-appropriate diabetes information packs containing published information in a folder that can be personalized by children and young people with pens and stickers. Resources have been designed for children/young people 6-10; 11-15; and 16-18 years.

To evaluate the information resources, we designed a pragmatic randomized controlled trial to assess the effectiveness, cost effectiveness, and implementation in routine practice of individually tailored, age-appropriate diabetes diaries and information packs for children and young people age 6-18years, compared with currently available standard practice.

Children and young people will be stratified by gender, length of time since diagnosis (< 2years and > 2years) and age (6-10; 11-15; and 16-18 years). The following data will be collected at baseline, 3 and 6 months: PedsQL (generic, diabetes and parent versions), and EQ-5 D (parent and child); NHS resource use and process data (questionnaire and interview). Baseline and subsequent HbA1c measurements, blood glucose meter use, readings and insulin dose will be taken from routine test results and hand-held records when attending routine 3-4 monthly clinic visits.

The primary outcome measure is diabetes self-efficacy and quality-of-life (Diabetes PedsQL). Secondary outcomes include: HbA1c, generic quality of life, routinely collected NHS/child-held data, costs, service use, acceptability and utility.

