### Stage 2. Diabetes diaries and information pack development

#### Expert clinical advisory group

Towards the end of phase 1, we convened an expert clinical group to discuss what gaps existed in current children's diabetes information, and what new information could be produced within the study budget and time constraints. It was decided that evidence concerning preferred formats and presentation of age-appropriate key health messages would be used to design and develop a series of age-appropriate children's diabetes diaries that record daily insulin management and blood glucose measurements, and carbohydrate counting sheets. In addition, the diary would be central to an age-appropriate information pack of existing diabetes and diabetes-related information resources that were considered high quality in terms of content and identified by children and young people in focus groups and interviews as being attractive and relevant to them in terms of content and presentation.

Evidence from stage 1 (ongoing literature review and discourse analysis) has been used as an empirical basis for developing the age appropriate diabetes diaries and information packs. The diabetes diaries and information pack were designed in conjunction with children/young people, parents, healthcare professionals, and a children's medical illustrator.

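### Secondary meter-use and glucose data can be ascertained differently by arm: meter checks are at the discretion of clinic teams who can know the allocation, and hand-held records may include the trial diary

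*Protocol article*

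**What the plan says.** - **Meter check.** The section *Baseline, 3 and 6 month data collection* states: "Blood glucose meters will be checked for the previous 250 blood glucose records if considered appropriate by the clinician". The sentence then adds a second condition: "and if used as part of routine clinical practice". The check therefore depends on both site practice and clinician judgement, and its extent is a number of readings with no calendar limit.
- **Who collects.** The same section says that HbA1c and the routine NHS and child-held data "will be collected by the clinicians/diabetes nurse specialists/MCRN nurses, or researchers where appropriate".
- **Other source.** The abstract (*Methods/Design*) says that "blood glucose meter use, readings and insulin dose will be taken from routine test results and hand-held records" at routine clinic visits every 3 to 4 months.
- **What the intervention is.** *Expert clinical advisory group* describes a series of "diabetes diaries that record daily insulin management and blood glucose measurements". Under *Group 1 - Information intervention* the diary and pack are "introduced by nurses/doctors and as appropriate other multi-disciplinary team members in clinic during routine visits".
- **Comparator.** *Group 2-Standard practice* is usual care. The form of the control children's own records is not described.
- **Status of the data.** *Secondary outcome measures* lists, after HbA1c and generic quality of life, "routinely collected NHS/child-held data, costs, service use, acceptability/utility". *Conceptual and methodological frameworks* names better meter use and insulin management as the purpose of introducing the resources.

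**The concern.** A between-arm comparison of meter use or glucose readings is fair only if the data are obtained in the same way in both arms. Three features of the collection rule work against that.

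1. **Selective checking.** A clinician who can know the allocation decides whether a meter is read. That decision can be influenced by the arm, by how well controlled the child appears, or by both. The missing data would then be related to arm and outcome, and no later analysis can recover a meter that was never read.
2. **Recording mistaken for testing.** If intervention children write in the new diary and controls use whatever they already have, the hand-held records may be more complete in one arm. More entries could then look like more testing.
3. **A count is not a period.** The calendar time that 250 readings cover depends on how often the child tests, which is itself one of the behaviours of interest. For infrequent testers it can extend to before randomisation.

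At stake is whether the trial can say anything reliable about meter use, a behaviour that the intervention is meant to change.

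**Working it through.** The protocol gives no derivation for the figure of 250, so there is no stated result to reproduce. Points 1 and 2 rest on reading the sections together; point 3 is arithmetic.

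**1. Discretion and knowledge of allocation.** *Site selection and preparation* and *Group 1* have clinic nurses and doctors tailor and introduce the pack. The data-collection section leaves the meter check to the clinician and allows clinicians and diabetes nurses to collect the data. No section describes blinded assessment or a rule that every meter be read. The site-practice condition should not itself differ by arm, because children are randomised individually. The clinician-judgement condition can.

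**2. Recording completeness.** Let the true testing rate be the same in both arms, and let the proportion of tests written down be cI (intervention) and cC (control). The apparent ratio of testing is cI / cC. The protocol gives neither value. With cC assumed to be 60%:
- cI = 60% gives 0.60/0.60 = 1.00
- cI = 70% gives 0.70/0.60 = 1.17
- cI = 80% gives 0.80/0.60 = 1.33

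These values show the mechanism only. They are not an estimate for this trial.

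**3. Period covered by 250 readings.**
- Days covered = 250 / (readings per day). Readings per day is not in the protocol; 1 to 8 is assumed.
- Time since randomisation, taking it to be at baseline: 91.3 days at 3 months, 121.7 at 4 months and 182.6 at 6 months.
- Break-even rate = 250 / (days since randomisation). It is 250/91.3 = 2.74 per day at 3 months, 250/121.7 = 2.05 at 4 months and 250/182.6 = 1.37 at 6 months.
- Share of readings before randomisation = 1 - (days since randomisation × rate) / 250, or zero if negative.

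| Readings/day | Days covered | Before randomisation, 3-month check | Before randomisation, 6-month check |
|---|---|---|---|
| 1 | 250 | 158.7 days (63%) | 67.4 days (27%) |
| 2 | 125 | 33.7 days (27%) | none |
| 3 | 83.3 | none | none |
| 4 | 62.5 | none | none |
| 8 | 31.2 | none | none |

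**4. Would a fixed window fit within the planned check?** For 28 days, 250/28 = 8.9 readings per day. The planned 250 readings therefore cover a 28-day window for any child testing up to about 8.9 times a day. At 3 months that window opens about 91.3 - 28 = 63.3 days after randomisation.

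**The case against.** The strongest reply is that this is a pragmatic trial using routine data for one loosely named component of the secondary outcomes, and that the section says which records are looked at, not how they will be analysed. If readings carry dates, tests per day follow from 250 divided by the days spanned, and an analysis plan could restrict the readings to a fixed period. Much of this stands. The choice of analysis window could be settled elsewhere, and it would be wrong to say that the count cannot show testing frequency.

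A reader might also infer that the hand-held records are the intervention diary. The protocol does not say so: it names routine test results as a second source and leaves the control arm's records undescribed. It supports only that the diary may serve as the hand-held record in the intervention arm.

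Nor does the protocol support the reading that pre-randomisation data affect most children. At three or more tests a day there is no overlap at either visit, and at 6 months, the time point of the main hypothesis, even two a day gives none.

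The reply does not meet the discretionary check. That is a stated collection rule, and an analysis plan cannot restore unread meters or equalise the completeness of written records.

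**Conclusion.** The point holds for the secondary meter-use and glucose data, and with more caution for insulin dose. As written, the plan allows ascertainment to depend on arm through clinician discretion, and possibly through differences in hand-held recording. The first follows directly from the text. The second depends on intervention children using the trial diary as their hand-held record, which is plausible but not stated.

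The size of either bias cannot be computed from the protocol. The overlap with the period before randomisation depends on all 250 readings being used and on testing rates below about 2.7 a day at 3 months or 1.4 at 6 months, and the protocol gives no testing rate.

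The primary Diabetes PedsQL score and HbA1c as a test result are unaffected, so the concern should not be read as a threat to the trial's main conclusion.

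**What to change.** - **Reading meters.** At sites that read meters routinely, read the meter of every trial child in both arms at each visit, whatever the clinician's view. This is a data-collection rule and changes no treatment.
- **Deriving outcomes.** Take tests per day and glucose readings from time-stamped meter memory over one fixed calendar window before each visit, with follow-up windows wholly after randomisation. Twenty-eight days is one workable choice.
- **Written records.** Do not use diary or hand-held entries to compare meter use or glucose readings between arms.
- **Insulin dose.** It may still come from hand-held or clinic records, since a meter rule supplies no replacement source. Report it with completeness by arm and interpret it cautiously.

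The cost is a little more data collection, a date filter, and no meter outcome at sites that do not read meters. The collection rule needs to be in place before follow-up visits begin, because unread meters cannot be recovered later.
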